## Methods/design

This study uses a randomized, two-group (experimental vs. attention control) design with three measurement periods: pre-intervention, end of treatment (3 months) and long-term follow-up (12 months). Smoking parents are recruited through urban pediatric healthcare clinics. The primary outcome of interest is child SHSe and the secondary outcome of interest is parent smoking abstinence. The study design is guided by CONSORT criteria
[23] and is approved by the relevant Institutional Review Boards (Temple University protocol number 20045). In the clinics, providers will ask parents about child SHSe, provide information on the harms of child SHSe and on the benefits of reducing child SHSe, and refer parents to cessation resources that include the KiSS program. Eligible parents are randomized either to an individual behavioral telephone counseling intervention that focuses on reducing child SHSe and parent smoking cessation or (b) an individual telephone health education attention control intervention that focuses on improving family nutrition on a budget.

### Participants

The pediatric clinics from which the sample will be drawn service predominantly low-income, racial- and ethnic-minority families. Eligibility inclusion criteria for parents are: Received pediatric clinic-level intervention, English-speaking, aged 18 years or older, report daily smoking, report that a child in the home under the age of 11-years old is exposed daily to cigarettes in the home/car. Exclusion criteria include patient-reported psychiatric disturbance, pregnancy, or consumption of three or more alcoholic beverages per day. Figure 
1 shows the participant flow through clinic intervention, enrollment, intervention, and data collection.

**Figure 1 F1:**
[figure not shown]
Flowchart of recruitment, intervention and assessment for Kids Safe & Smokefree (KiSS) trial.

### Procedures

Pediatric healthcare providers in partnering clinics will be trained to provide brief advice about child SHSe and to refer assenting parents to the KiSS research staff. The sampling frame includes any parent who meets the eligibility requirements following receipt of the clinic intervention and referral. Trained research assistants consent eligible participants and collect self-report data at baseline, 3-month end-of-treatment, and 12-month follow-up via structured telephone interviews. Interviewers are blind to participants’ intervention condition. Various procedures are used to reduce attrition, including reminder postcards and text messages, flexible scheduling, and financial retention incentives for completing different phases of the study.

Randomization is stratified by site and race using randomized permuted blocks of varying lengths. Because site and strata were not fixed design characteristics, the maximum number of allocations was generated within each combination of site and stratum. The project biostatistician provided the allocations to the data collection team in opaque sealed security envelopes. Randomization was seeded using values obtained from random.org. Participants are randomized prior to an orientation home visit that follows the baseline interview. Once a home visit appointment is confirmed, a research assistant takes the top envelope from the allocation pile to bring to the home visit. The envelope is opened immediately prior to the home visit to reveal the condition.

During the home visit, participants receive a binder with materials that are relevant to their assigned intervention condition and they provide a sample of the child’s urine for baseline cotinine assessment. The child’s urine is collected again at the 12-month follow-up. Parents who report quitting smoking at 12-month follow-up are asked to provide a biospecimen for cotinine verification of quit status.

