**Methods/design:**

This trial uses a randomized, two-group design with three measurement periods: pre-intervention, end of treatment and 12-month follow-up. Smoking parents of children < 11-years-old are recruited from pediatric clinics. The clinic-level intervention includes integrating tobacco intervention guideline prompts into electronic health record screens. The prompts guide providers to ask all parents about child SHSe, advise about SHSe harms, and refer smokers to cessation resources. After receiving clinic intervention, eligible parents are randomized to receive: (a) a 3-month telephone-based behavioral counseling intervention designed to promote reduction in child SHSe, parent smoking cessation, and navigation to access nicotine replacement therapy or cessation medication or (b) an attention control nutrition education intervention. Healthcare providers and assessors are blind to group assignment. Cotinine is used to bioverify child SHSe (primary outcome) and parent quit status.

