[11,22] intervention. Therefore, counselors guide participants to break down smoking behavior change efforts into manageable steps in preparation for cessation by utilizing a behavioral shaping approach that reinforces progress on short-term goals to maintain motivation and confidence in achieving long-term smoking cessation outcomes. For example, smokers will first focus on child health and SHSe reduction (e.g., setting dates to establish home smoking bans) and use behavioral strategies to facilitate the short-term goal in preparation for quitting smoking and maintaining smoking abstinence.

The KiSS BC program is distinct from FRESH in two key dimensions. First, KiSS counselors review and reinforce the information conveyed by the pediatric healthcare provider—an intervention component that is absent from FRESH. Second, KiSS counselors navigate participants to additional smoking cessation services that are publically available. For example, counselors will encourage and provide logistical support that helps participants to access smoking quitlines and nicotine replacement therapy and prescription cessation medications. Counselors will educate participants about existing resources, how to access them, and problem-solve barriers to adherence to cessation medication.

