##### Attention control: nutrition education (AAR + AC)

Trained health counselors deliver the AC intervention. Training, intervention orientation, and telephone counseling procedures mirror those of the BC arm, but focus on improving nutrition on a budget (e.g., learning about national guidelines related to fruit and vegetable consumption). The purpose of the AAR + AC group is to equate attention and contact between the two experimental conditions while providing distinctly different intervention content. Included in the home visit materials is a tool kit developed by Sesame Street Workshop, *Food for Thought: Eating Well on a Budget*[27]. The kit includes DVD videos on nutrition on a budget, nutrition guidelines, recipe cards, and colorful books, activity suggestions, and videos on fruit and vegetable consumption for children.

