### Measures

#### Primary and secondary outcome variables

Participant self-report data is collected via telephone interviews. The primary dependent variable—child SHSe—will be measured in two ways. First, child cotinine will be collected in urine samples taken at baseline and the 12-month follow-up. Second, child SHSe will be measured by parental report of the number of cigarettes to which the child is exposed each day during the 7 days prior to all assessment periods
[28]. The secondary dependent variable—parent’s smoking cessation—will be assessed via parent-reported 7-day point prevalence abstinence for the 7 days prior to assessment at 3- and 12-month follow-up. The 12-month parent cessation report will be cotinine-verified.

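### Cotinine alone verifies parents' 12-month quitting, so abstinent parents still on nicotine replacement can fail the check, probably more often in the AAR + BC arm

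*Protocol article*

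**What the plan says.** Aim 2 of the protocol article concerns smoking abstinence. Under Primary and secondary outcome variables, parent cessation "will be assessed via parent-reported 7-day point prevalence abstinence for the 7 days prior to assessment at 3- and 12-month follow-up". The same section adds: "The 12-month parent cessation report will be cotinine-verified". Procedures says how: "Parents who report quitting smoking at 12-month follow-up are asked to provide a biospecimen for cotinine verification of quit status". The Abstract repeats it: "Cotinine is used to bioverify child SHSe (primary outcome) and parent quit status". No other marker is named for parents.

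Nicotine replacement appears at two levels:

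- **Both arms, before randomization.** The section on the clinic intervention (both groups) has providers counsel smokers, give a printout of cessation resources that covers replacement products, and supply medication referral, including for a replacement prescription.
- **AAR + BC only, after randomization.** The Abstract lists "navigation to access nicotine replacement therapy or cessation medication" as part of the counseling arm. The section on behavioral counseling has counselors give logistical support that "helps participants to access smoking quitlines and nicotine replacement therapy and prescription cessation medications", and work through barriers to adherence. The Background likewise describes the behavioral intervention as easing access to no-cost replacement and its effective use. The attention control mirrors the counseling procedures "but focus on improving nutrition on a budget".

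The Analytic plan uses logistic regression for the parent outcome and takes a significant positive AAR + BC coefficient as evidence for hypothesis 2.

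**The concern.** Cotinine is formed from nicotine whatever its source. A positive result in a parent who reports having quit may mean continued smoking, or abstinence from smoking with current use of replacement. The second parent has met the stated outcome and would still fail the check.

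This matters because the randomized difference includes help to obtain and keep using replacement. If that help leads more AAR + BC quitters to be using replacement when the specimen is taken, the failures are unevenly spread between arms. The verified quit rate is then lowered more in AAR + BC, and the treatment coefficient is pulled towards zero. The 12-month part of hypothesis 2 is at stake, and with it the cessation side of the Aim 3 mediation analysis where that uses the verified outcome.

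**Working it through.** **Is the mechanism in the text?**

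1. The outcome is abstinence from smoking (Aim 2; Primary and secondary outcome variables).
2. The only verifier is cotinine (Abstract; Procedures; Primary and secondary outcome variables).
3. Active navigation to replacement after randomization is described for AAR + BC and not for AAR + AC (the two intervention sections).
4. Counseling runs over 12 weeks, about 3 months, and verification is at 12 months. The gap is 12 − 3 = about 9 months.
5. The 3-month report is not cotinine-verified, so it is untouched. Child exposure is measured separately.

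**How large could it be?** The protocol gives no quit rate, no rate of replacement use and no power for the parent outcome, so there is no figure to reproduce. Every rate below is an assumption.

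Formulas, assuming each abstinent replacement user fails the check and is counted as smoking:

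- verified quit rate = true quit rate × (1 − share of true quitters on replacement at 12 months)
- odds ratio = [p_BC / (1 − p_BC)] / [p_AC / (1 − p_AC)]

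True quit rates assumed 20% (BC) and 10% (AC). Power is for two proportions at an assumed two-sided 0.05, with the 166 per arm of the Power analysis and with 116 per arm (166 × 0.70, the upper attrition figure).

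| Quitters on replacement, BC / AC | Verified rates | Difference (points) | Odds ratio | Power, 166 per arm | Power, 116 per arm |
|---|---|---|---|---|---|
| 0% / 0% | 20.0% / 10.0% | 10.0 | 2.25 | 0.73 | 0.57 |
| 5% / 2% | 19.0% / 9.8% | 9.2 | 2.16 | 0.67 | 0.51 |
| 10% / 5% | 18.0% / 9.5% | 8.5 | 2.09 | 0.61 | 0.47 |
| 20% / 5% | 16.0% / 9.5% | 6.5 | 1.81 | 0.43 | 0.32 |
| 30% / 10% | 14.0% / 9.0% | 5.0 | 1.65 | 0.30 | 0.22 |
| 10% / 10% | 18.0% / 9.0% | 9.0 | 2.22 | 0.67 | 0.52 |

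Worked row (20% / 5%): 0.20 × 0.80 = 0.160 and 0.10 × 0.95 = 0.095; (0.160/0.840) / (0.095/0.905) = 1.81.

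With lower assumed true rates, 12% and 6%:

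- No replacement use: (0.12/0.88) / (0.06/0.94) = 2.14; difference 6.0 points.
- 20% / 5%: 0.12 × 0.80 = 0.096 and 0.06 × 0.95 = 0.057; odds ratio 1.76; difference 3.9 points.
- 30% / 10%: 0.084 and 0.054; odds ratio 1.61; difference 3.0 points.

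The last row of the table shows that the odds ratio hardly moves when use is equal in the arms, although some power is lost. Material bias in the odds ratio needs use to differ by arm. With no use at 12 months there is no bias.

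**The case against.** Four points can be made for the plan.

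- **No classification rule is stated.** A reader might infer that the plan counts every cotinine-positive parent as a smoker, without exception. The article does not say so: it gives no cut-off, no parent specimen type and no consequence of a positive result. A condensed article may leave these to the full protocol or analysis plan, and one of those may handle replacement users. This stands. What remains is the choice the article does fix: a marker that cannot tell the two groups apart, as the only check in a trial that promotes replacement in one arm. If recent use is not recorded when the specimen is taken, no later analysis plan can recover it.
- **The control arm also has a route to replacement.** A reader might infer that AAR + AC parents get no more than a printed list. The clinic section contradicts that: both groups are counseled and offered prescription referral. This stands, and it narrows the contrast. It does not remove the navigation described only for AAR + BC.
- **Timing.** Verification comes about nine months after counseling ends, so few parents may still be using replacement. This stands and limits the size. Against it, counseling deliberately works on the child's exposure before quitting, and the outcome is point prevalence at 12 months, so later quit attempts count too.
- **Limited stakes.** This is one time point of a secondary outcome, and the bias described runs against the intervention. This stands, but a real effect could still be missed or understated.

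**Conclusion.** The point holds in a limited form. Verifying a smoking-abstinence outcome by cotinine alone can fail abstinent parents who still use replacement, and the design makes this more likely in AAR + BC. The direction is towards no effect on the 12-month part of hypothesis 2.

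The size cannot be derived from the document. In the illustrations it runs from nothing, through a small shift (odds ratio 2.25 to 2.16), to a substantial one (2.25 to 1.65). All of these rest on assumed quit rates and replacement use, and on positive parents being counted as smokers.

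A reader might go further and conclude that the comparison is biased, or that misclassification falls mainly in AAR + BC. The document reports no replacement use by arm, so an excess in AAR + BC is a reasonable expectation and not a documented fact. The 3-month parent outcome and the child outcome are unaffected. This is worth correcting because the correction is cheap and the information cannot be collected afterwards.

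**What to change.** 1. At the 12-month interview, ask parents in both arms about nicotine replacement and other non-combusted nicotine use in the days before the specimen.
2. State in Procedures and in Primary and secondary outcome variables that a positive cotinine in a self-reported quitter with such use is non-informative and does not by itself reclassify the parent as a smoker.
3. Report the 12-month hypothesis 2 result twice, with these parents counted as quit and with all of them counted as smoking, using the same rule in both arms. The two results bracket the answer if the share of these parents who are truly abstinent is similar in the two arms.
4. Optionally, where stored specimens allow, test these few parents for a tobacco-specific alkaloid such as anabasine.

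The cost is one interview item, one sentence of definition and one further analysis, plus a small number of assays if step 4 is taken. The downside is that, without the assay, these parents have no biochemical proof of quitting. They may be more frequent in AAR + BC, so counting them as quit by self-report could favour that arm. For that reason neither result should be reported without the other.

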#### Interventions

As part of the KiSS project, participating clinics have modified their electronic health records (EHR) to include prompts to healthcare providers to address parental smoking and to record information on SHSe in the EHR. The KiSS PIs coordinate pediatric providers’ training and ongoing AAR monitoring in collaboration with clinic liaison co-investigators. During a clinic visit, any parent accompanying the child who is a smoker is referred to KiSS. Thus, all study participants receive clinic-level intervention related to child SHSe, as recommended by the American Academy of Pediatrics, prior to randomization. Once randomized, participants will receive either additional individual-level intervention related to their smoking and child SHSe or education about nutrition on a budget, depending on their assignment.

##### Clinic intervention using AAR (both groups)

The clinic-level component of KiSS was modeled on the guiding principles underlying the standalone Clinical Effort Against Secondhand Smoke Exposure (CEASE) program for addressing parental smoking in pediatric clinics
[24,25]. However, unlike CEASE, the KiSS AAR intervention is integrated within each clinic’s EHR system. Key goals of the KiSS AAR intervention are to (1) identify parents who smoke in the child's home, (2) counsel smokers about tobacco use and establishing no smoking policies around children; (3) provide smoking intervention and medication referral resources to the parent (including referral to the KiSS project and NRT prescription); (4) record information in the EHR to facilitate ongoing follow-up regarding the child’s SHSe. During a pediatric clinic visit, the healthcare provider is prompted to ask the parent about the child’s exposure to SHS, enter the diagnosis into the health record, and advise the parent about the potential harms of child SHSe and benefits of reducing exposure. Finally, the provider gives parents a brochure, *Secondhand Tobacco Smoke and the Health of Your Family* (EPA 402/F/09-044) from the Environmental Protection Agency, a printout of local and state resources for people who are “Ready to Quit” that includes information about cessation medication and nicotine replacement products, and inform parents about the KiSS program and refers assenting parent to KiSS staff (e.g., via EHR auto-fax). There are two primary differences between the KiSS AAR and CEASE: KiSS works within the EHR rather than using any paper-based systems to prompt AAR steps and shifts the burden of advice, counseling and navigation to nicotine replacement therapy and medication from the pediatric provider to a behavioral health counselor.

Integrating KiSS AAR into routine clinic operations involves adoption, implementation, and maintenance phases. During adoption, the clinic liaisons meet with the investigators to design and implement the AAR interface in clinics’ EHR system for identifying children exposed to SHS and referring interested parents to KiSS. The program is then implemented in each participating clinic using an academic detailing approach, including talking with providers about the program, promoting AAR steps to improve the quality of patient care, installing KiSS program posters and placing brochures in waiting and clinic exam rooms. In the maintenance phase, clinic liaisons receive quarterly reports on clinic performance that includes number of referrals received and information on whether referred parents report receiving oral and written materials on the harms of child SHSe, the benefits of reducing SHS, and local smoking cessation support services.

##### Smoking intervention: behavioral counseling (AAR + BC)

Trained health counselors deliver the BC intervention. Training consists of role-playing, didactic sessions, and readings on nicotine dependence and intervention. Counselors learn about the provision of standard cognitive-behavioral counseling strategies to facilitate smoking behavior change, how to help participants to set short-term treatment goals, how to provide social support and positive reinforcement, how to facilitate problem solving to overcome behavior change barriers, and how to provide guidance and advice about existing services and coverage to obtain nicotine replacement products. Counselors also receive weekly supervision to review specific cases and adherence to treatment protocols. The telephone counseling sessions are audiotaped and a subset of the sessions are reviewed to ensure adherence to the manualized treatment protocol.

Prior to beginning telephone counseling related to smoking and child SHSe, KiSS staff members visit participants in their home to provide an orientation to the intervention program, share a program binder that is used in conjunction with the telephone counseling, and collect a baseline urine sample from the target child for cotinine assessment. The BC intervention consists of five telephone-counseling sessions, interspersed with “check-in” retention calls, delivered over 12 weeks. The BC intervention explicitly extends pediatric provider advice parents received at a recent clinic visit. The BC intervention consists of evidence-based strategies to promote SHSe reduction, smoking cessation and relapse prevention, including health education and social support to guide child SHSe-reduction efforts, cognitive-behavioral counseling to promote coping skills acquisition for smoking urge and stress management, and motivational interviewing techniques to facilitate collaborative, personalized treatment. The intervention process is guided by ecological and associative learning theories (e.g., Social Cognitive Theory; Behavioral Ecological Model
[12,26]) and uses components from the FRESH (Family Rules for Establishing Smoke-free Homes)
[11,22] intervention. Therefore, counselors guide participants to break down smoking behavior change efforts into manageable steps in preparation for cessation by utilizing a behavioral shaping approach that reinforces progress on short-term goals to maintain motivation and confidence in achieving long-term smoking cessation outcomes. For example, smokers will first focus on child health and SHSe reduction (e.g., setting dates to establish home smoking bans) and use behavioral strategies to facilitate the short-term goal in preparation for quitting smoking and maintaining smoking abstinence.

The KiSS BC program is distinct from FRESH in two key dimensions. First, KiSS counselors review and reinforce the information conveyed by the pediatric healthcare provider—an intervention component that is absent from FRESH. Second, KiSS counselors navigate participants to additional smoking cessation services that are publically available. For example, counselors will encourage and provide logistical support that helps participants to access smoking quitlines and nicotine replacement therapy and prescription cessation medications. Counselors will educate participants about existing resources, how to access them, and problem-solve barriers to adherence to cessation medication.

##### Attention control: nutrition education (AAR + AC)

Trained health counselors deliver the AC intervention. Training, intervention orientation, and telephone counseling procedures mirror those of the BC arm, but focus on improving nutrition on a budget (e.g., learning about national guidelines related to fruit and vegetable consumption). The purpose of the AAR + AC group is to equate attention and contact between the two experimental conditions while providing distinctly different intervention content. Included in the home visit materials is a tool kit developed by Sesame Street Workshop, *Food for Thought: Eating Well on a Budget*[27]. The kit includes DVD videos on nutrition on a budget, nutrition guidelines, recipe cards, and colorful books, activity suggestions, and videos on fruit and vegetable consumption for children.

